#### Motor development

To assess motor development of toddlers, the Movement ABC2 test will be carried out (only applicable for toddlers of > 3.0 years) [36]. Standard Scores on each part of the Movement ABC2 assessment battery will be calculated. Thereafter, a Total Test Score for each toddler will be determined.

### Trial status

PS@HW is registered through the Netherlands Trial Register (NTR): NL5850.

### Planned statistical analysis

The sample size is based on a medium effect size (Cohen’s d: 0.50), a 1-sided alpha of 5% and a power of 80%, taken into account a design effect (mean cluster size = 3, ICC: 0.05) and a 10% drop-out rate.

Descriptive statistics (percentages, mean ± SD, or median (IQR)) will be used to describe the characteristic of the study population.

Mixed Model analyses will be used for the effect evaluation with primary and secondary outcome measures at the level of ECEC teachers, toddlers and their parents. Time, treatment (intervention or control group) and their interaction are fixed factors. Subject and location will be included as random factors to take into account the clustered data structure.

For the purpose of implementing the preschool-based intervention on organizational level, a process evaluation focusing on the acceptance, satisfaction and improvements of the intervention will be performed.

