#### A Healthy Start

The national program ‘A Healthy Start’ is an initiative of the Dutch Ministry of Health, Welfare and Sport and the Ministry of Social Affairs and Employment. It is developed by 7 renowned Dutch knowledge centres (Knowledge Centre for Sports Netherlands, Netherlands Youth Institute, Pharos Dutch Centre of Expertise on Health Disparities, the Netherlands Nutrition Centre, National Institute for Public Health and the Environment, the Netherlands Organisation for applied scientific research TNO, and VeiligheidNL). Train-the-trainer courses are organized for ECEC teachers and ECEC teachers in training. ‘A Healthy Start’ focusses on the development of knowledge and practices about nutrition, physical activity and education of ECEC teachers. The national program consists of a basic model and 4 in-depth modules. The basic module includes 3 face-to-face meetings of 2.5 h each. The in-depth modules, each between 4 and 6 h, are optional and concern the themes Nutrition, Physical Activity, Weight and Safe Behaviour & Safe Environment. Special attention is given to the diversity of children and their parents [16]. For the intervention of PS@HW, research staff and 3 coaches of child care organization Impuls, who met criteria of the train-the-trainer course for the national program, composed a modified version of ‘A Healthy Start’. The modified version includes theory and practical assignments of the basic module and in-depth modules Nutrition, Physical Activity and Weight. Three face-to-face meetings of 2 h will be organized for 8 groups of ECEC teachers (in total 24 meetings). Each meeting will be led by a coach of child care organization Impuls and a member of the research staff. In the first meeting ECEC teachers will reflect on their own lifestyle and on the topic healthy lifestyle in their organization. Furthermore, theory about the Dutch food-based dietary guidelines (2015) will be discussed. The second meeting focusses on the interaction with toddlers and a healthy lifestyle, and the role of ECEC teachers in setting a healthy example. In the third meeting, the interaction with parents and a healthy lifestyle will be discussed.

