#### PLAYgrounds for Toddlers

The initial ‘PLAYgrounds’ program concerns a physical education based playground program for primary schools to improve physical activity levels of children during recess times. The program consists of a multi-component alteration of the schools’ playground. In addition, the playground usage is stimulated by altered time management of recess times, teachers stimulating physical activity and a modification of the physical education content. ‘PLAYgrounds’ is proven to be effective in primary schools [17, 18]. For PS@HW, the program was adapted to the context and target group on preschools of child care organization Impuls. This ‘PLAYgrounds’ program for toddlers focusses on the amount and type of physical activity and the prompts of ECEC teachers within the possibilities of the outdoor space and availability of material in preschools. Two training sessions and 1 evaluation session will be organized for in total 4 groups of ECEC teachers. In addition, a trainer will visit each preschool in the intervention group between the training sessions to give specific instructions for improvement (coaching on the job) to the local team of ECEC teachers.

In PS@HW, ‘A Healthy Start’ and ‘PLAYgrounds for Toddlers’ have a complementary role. The multi-component and multilevel programs share a focus on providing a healthy and active environment for toddlers and the role of ECEC teachers to set a healthy example. The interventions will be applied consecutively, in order not to overload ECEC teachers. Attendance records will be used to determine the adherence of ECEC teachers to the intervention. All participants who will attend at least 2 meeting of ‘A Healthy Start’ and 1 meeting of ‘PLAYgrounds for Toddlers’ will receive certificates.

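### The planned model has no location-by-time random term, so the time-by-treatment interaction gets no allowance for changes that cluster within preschools

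*Protocol article*

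**What the plan says.** The analysis model is set out in the protocol article under Planned statistical analysis. The fixed part reads "Time, treatment (intervention or control group) and their interaction are fixed factors". The random part reads "Subject and location will be included as random factors to take into account the clustered data structure". No location-by-time term or random slope is named. The text does not use the word intercept, and it does not say which coefficient is the tested effect.

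The sample-size sentence in the same section allows for clustering with "mean cluster size = 3, ICC: 0.05". It uses "a 1-sided alpha of 5% and a power of 80" percent.

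Other sections supply the context. Preschools, not individuals, were allocated (Study design and setting). The sample is 41 preschools with 115 teachers and 249 toddlers with their parents, and four preschools were combined for allocation because they shared a building or playground (Recruitment). Teachers complete questionnaires at baseline, 4 and 9 months, parents at baseline and 9 months (Procedures and outcome measures). A trainer visits each intervention preschool to coach its team on the job (PLAYgrounds for Toddlers).

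**The concern.** The random part is given a stated purpose: to handle clustering. In a model with time, treatment and their interaction, the effect of the intervention is normally read from the interaction, which compares changes from baseline between arms. A location intercept shifts all of a preschool's measurements by the same amount at every visit, so it subtracts out of every change. It therefore cannot represent preschools that improve more or less than others.

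That is the kind of clustering this design could well produce. Teams are coached together on site, and toddlers in one preschool share the same teachers. If it is present and unmodelled, confidence intervals are too narrow and the type I error exceeds its nominal level. The exposure grows with the number of people per preschool, so it is larger for toddlers and parents than for teachers.

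**Working it through.** **Inputs from the article.** Design-effect inputs: m = 3, ICC = 0.05. Average cluster sizes: 115 / 41 = 2.8 teachers and 249 / 41 = 6.1 toddlers, rounded below to 3 and 6. The only alpha stated is one-sided 5%.

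**Assumptions.** Random factors means random intercepts; the tested effect is the baseline-to-9-month interaction; clusters are equal in size; 40 preschools are split 20 per arm (the allocation ratio is not stated). The within-preschool correlation of change, ρ, is not given, so a range is used.

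**1. The plan's own allowance.** Design effect = 1 + (3 − 1) × 0.05 = 1.10. The article gives inputs but no target number, so there is no stated sample size to reproduce.

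**2. Cancellation.** For person j in preschool i at visit t, the random part is a_i + b_ij + e_ijt. The change from baseline to the last visit T is e_ijT − e_ij0; both a_i and b_ij are gone. With K preschools per arm and m people in each, the model's variance of the interaction is 2 × 2σ² / (K × m). With σ² = 0.5 and K = 20:

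- Teachers, m = 3: sqrt(2 / 60) = 0.1826.
- Toddlers, m = 6: sqrt(2 / 120) = 0.1291.

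An exact generalised least squares calculation gave the same two values whether the location variance was 0, 0.05 or 0.5.

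**3. What is left out.** Add a location-by-time deviation c_it with variance τ², and let σ² + τ² = 0.5. The changes of two people in the same preschool then correlate at ρ = τ² / (τ² + σ²). The variance of the interaction is multiplied by 1 + (m − 1)ρ, while the intercept-only model still reports the values in step 2. So true SE / reported SE = sqrt(1 + (m − 1)ρ), and the true one-sided error is 1 − Φ(1.645 / ratio).

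| ρ (assumed) | Teachers (m = 3): SE ratio | One-sided error | Toddlers (m = 6): SE ratio | One-sided error |
|---|---|---|---|---|
| 0 | 1.00 | 5.0% | 1.00 | 5.0% |
| 0.05 | 1.05 | 5.8% | 1.12 | 7.1% |
| 0.10 | 1.10 | 6.7% | 1.22 | 9.0% |
| 0.20 | 1.18 | 8.2% | 1.41 | 12.2% |

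Example: for toddlers at ρ = 0.05, sqrt(1 + 5 × 0.05) = 1.118; 1.645 / 1.118 = 1.471; upper tail 7.1%. If the tests were two-sided at 5%, the errors at ρ = 0.05, 0.10 and 0.20 would be 6.2%, 7.4% and 9.8% for teachers and 8.0%, 11.0% and 16.6% for toddlers.

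**4. Check by fitting.** Restricted maximum likelihood fits of the intercept-only model to simulated data (120 runs per setting) agree at ρ = 0.20. The mean reported SE against the empirical SD was 0.181 against 0.210 for teachers, and 0.129 against 0.182 for toddlers. So few runs do not estimate error rates well, so the table rests on the formula.

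**The case against.** The strongest reply is that the fault is conditional and inferred. The article does not say intercepts, does not exclude a location-by-time term and does not name the tested coefficient. For a between-arm contrast at a single visit, the location intercept would count. A condensed article may leave the exact random structure and the degrees of freedom to an analysis plan that is not shown. This stands in part: the absence of a degrees-of-freedom method is no defect here. But the article does list the random factors and says what they are for, and on the ordinary reading they do not serve that purpose for the interaction.

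A reader might infer that the standard errors are too small as a matter of fact. The documents do not support that. If preschools differ only in level, ρ for change is zero and the planned standard error is correct. The ICC of 0.05 is a sample-size input, and applying it to change is an assumption.

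A reader might also take the larger figures as the size of the problem. The stated primary outcomes are all teacher outcomes, for which ρ = 0.05 adds about 0.8 percentage points to the one-sided error. The larger values belong to secondary outcomes or to higher assumed ρ.

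Finally, a reader might extend the point to the training groups, since the article plans 8 groups for A Healthy Start ("Three face-to-face meetings of 2 h will be organized for 8 groups of ECEC teachers (in total 24 meetings") and 4 for PLAYgrounds ("Two training sessions and 1 evaluation session will be organized for in total 4 groups of ECEC teachers"). Group sizes would require an allocation ratio that is not stated, group composition is not described, and no correlation within groups is given. This is not an error in the plan.

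**Conclusion.** The point holds in conditional form. As described, and read as random intercepts, the model makes no allowance for clustering in the time-by-treatment interaction, although the sample size was inflated for it. If changes correlate within preschools, the reported standard error is too small. At an assumed ρ of 0.05 the true standard error is about 5% larger than reported for teachers and 12% larger for toddlers. The effect on the primary outcomes is modest at that value, and it grows with ρ and with cluster size. Parents were recruited with the toddlers, so their cluster size and exposure are similar.

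The conclusion rests on the intercept-only reading, on the interaction being the tested effect, and on a ρ that the documents do not give. The figures also assume equal cluster sizes and complete data; with missing visits the cancellation is only approximate. It is worth correcting before analysis because the remedy needs no new data and protects the type I error.

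**What to change.** State the random structure in full and add a location-by-time random effect to the subject and location intercepts. Define location as the randomised unit, so that preschools combined for allocation share one level. Use small-sample degrees of freedom, such as Kenward-Roger or Satterthwaite. Name the interaction contrast that is tested.

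An alternative is to analyse follow-up scores adjusted for baseline, with a random location effect. This is a different estimator with its own standard error, not an equivalent of the interaction model. For teachers it should be a repeated-measures version, so that the 4-month data are kept.

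The cost is one more variance component and slightly wider confidence intervals. For teachers that component will often be estimated near zero. A moment-based approximation with 41 equal preschools, 2.8 teachers each and an assumed ρ of 0.05 puts the estimate at or below zero in about 32% of trials. In those trials the added term changes little.

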## Discussion

This study aims to evaluate the effect of a preschool-based intervention for ECEC teachers. It is hypothesized that the intervention will increase the knowledge, attitude and practices of ECEC teachers regarding healthy eating and physical activity and consequently the level of confidence in promoting healthy eating and physical activity of toddlers. The preschool-based intervention addresses the call for early intervention to prevent overweight and obesity and to minimize health inequalities.

Strengths include the randomized controlled study design and multi-component and multi-level character of the intervention. Moreover, the diverse study population is a strength. However, the study is limited in the ability to generalize the findings, as only preschools of 1 child care organization in Amsterdam are included.

## Abbreviations

BMI: Body Mass Index
CFAPQ: Child-care Food and Activity Practices Questionnaire
CFPQ: Comprehensive Feeding Practices Questionnaire
ECEC: Early Childhood Education and Care
PPAPP: Preschooler Physical Activity Parenting Practices
PS@HW: PreSchool@HealthyWeight
